### Plans for the Assessment and Collection of Outcomes

Participants will be assessed, enrolled, randomized, and followed up. Clinical and laboratory data will be collected by study staff.

### Plans to Promote Participant Retention

It has been anticipated that participants will be in the hospital during the treatment phase. Subsequent outpatient visits to the study site will be performed and timed with routine clinic appointments, as per the protocol.

### Data Management

The EDC system, REDCap, will be used for the collection of trial data. An input manual with details on the input methodology will be created. Chest CT images and chest radiographs taken when the research is suspended due to pneumonia onset are to be sent to the Center Hospital of the National Center for Global Health and Medicine by CD-ROM.

### Confidentiality

Any information that may identify a participant will be excluded from publicly presented data. Furthermore, all study-related information will be stored securely at each study site. All copies of clinical records, reports, data collection documentation, process documentation, and administrative forms will be identified through coded identification. Additionally, the principal physician will retain the stored records that relate to the proposed research for 5 years following the day the proposed research is completed.

### Storage of Biological Specimens

Serum and nasal swabs are to be stored in a freezer at a temperature of below −80°C.

The samples from the collaborating research implementing medical institutions will be sent to the National Center for Global Health and Medicine. Serum SARS-CoV-2 antibody values will be measured at the National Center for Global Health and Medicine laboratory, and SARS-CoV-2 PCR assays will be performed at the Tokyo Metropolitan Institute of Public Health. All samples will be stored for 5 years following the day the proposed research is completed.

### Statistical Methods

#### Sample Size

The sample size for the RACCO trial will be 90 patients (ie, n=45 for the ciclesonide group and n=45 patients for the symptomatic treatment group) to control for pneumonia onset and allow for the full analysis of study participants to complete the study.

Based on our experience, 35% of patients who have tested positive for COVID-19 without pneumonia symptoms will have pneumonia during the follow-up period. The necessary number of cases for a 2-sided α-level of 10% and power of 80% for cases with incidence percentages of 30%, 35%, 40%, and 50% in the standard treatment group and incidence percentages of 5%, 10%, 15%, and 20% in the trial treatment group are shown in Figure 3.

The effect of controlling the pneumonia onset percentage to 25% would mean that the drug is clinically effective. The numbers highlighted in grey in Figure 3 are the sample sizes necessary for detecting effects with a power of 80% in cases where a 25% pneumonia onset control is present. For example, if the pneumonia onset percentage of the standard treatment and trial treatment groups were hypothetically set to 35% and 10%, respectively, the required sample size would be 84. Factoring in cases where consent may be withdrawn during the trial or participants drop out, the target number of cases for the present research will be set at N=90. The target number of cases will be specified for each implementing medical institution.

**Figure 3 figure3:**
[figure not shown]
Sample size calculation. Numbers highlighted in grey represent the sample sizes necessary for detecting effects with a power of 80% in cases where a 25% pneumonia onset control is present.

#### Analysis Sets

This study will contain the following 3 analysis sets: the full analysis set, the per protocol set, and the safety analysis set. The full analysis set has been defined as research participants who have been registered in the proposed research, have been randomized, have had their baseline CT image data acquired, and have no serious protocol violations.

The per protocol set has been defined as research participants from the full analysis set after removing cases with the following serious protocol violations: selection criteria violations, exclusion criteria violations, prohibited drug violations, prohibited treatment violations, and a medicine administration compliance of below 90%.

In the safety analysis set, all participants will be analyzed.

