### Interventions

Participants will be randomized to 1 of the 2 treatment groups. In the ciclesonide group, a 400-µg dose of ALVESCO, which is manufactured by Teijin Pharma Limited, Japan, will be administered to patients with asymptomatic or mild COVID-19 3 times per day over a continuous 7-day period. The patients will also receive antitussives and antipyretics as needed. In the symptomatic treatment group, only antitussives and antipyretics will be administered to the patients as needed.

Ciclesonide has not been approved for COVID-19 treatment in Japan or internationally, and is used only for research purposes.

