### Relevant Concomitant Care Permitted or Prohibited During the Trial

The following drugs are prohibited during the research implementation period (ie, from consent acquisition to the final observation date): (1) orally or intravenously administered systemic adrenocortical steroids, (2) inhaled steroids other than inhaled ciclesonide, and (3) drugs that may have therapeutic effects against COVID-19 (eg, remdesivir, lopinavir/ritonavir compound drugs, favipiravir, interferon, and hydroxychloroquine).

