#### Statistical Methods for Primary and Secondary Outcomes

Analyses are to be conducted after drug administration to all patients has been completed and the data have been finalized. For all efficacy assessments, the full analysis set analysis will be set as the primary analysis, and the per protocol set analysis will be conducted as a reference. A safety analysis will also be conducted using the safety analysis set.

The distribution of research subject background data and the summary statistics in each analysis set will be calculated for each group. For nominal variables, category frequency and percentage will be shown for each group. For continuous variables, the summary statistics (ie, number of cases, average value, standard deviation, minimum value, median value, and maximum value) will be calculated for each group.

Intergroup comparisons will be performed with the Pearson Chi-squared test or Fisher exact test for nominal variables. The 2-tailed Student *t* test or Wilcoxon signed-rank test will be used for continuous variables. The significance level will be set at 10% for both sides.

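### As worded, the primary full analysis set excludes protocol violators and so coincides with the per protocol set; some exclusions arise after randomisation and can be linked to the outcome

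*Protocol article*

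**What the plan says.** All references are to the protocol article.

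- **Analysis Sets, full analysis set.** Patients must be registered and randomised, and must "have had their baseline CT image data acquired, and have no serious protocol violations".
- **Analysis Sets, per protocol set.** This is "research participants from the full analysis set after removing cases with the following serious protocol violations". The list covers selection and exclusion criteria violations and ends with "prohibited drug violations, prohibited treatment violations, and a medicine administration compliance of below 90" (per cent). No other or narrower meaning of a serious violation is given for the full analysis set.
- **Statistical Methods for Primary and Secondary Outcomes.** For every efficacy assessment, "the full analysis set analysis will be set as the primary analysis, and the per protocol set analysis will be conducted as a reference".
- **Interventions.** Ciclesonide is given "3 times per day over a continuous 7-day period". In the control arm "only antitussives and antipyretics will be administered to the patients as needed".
- **Relevant Concomitant Care Permitted or Prohibited During the Trial.** Systemic steroids, other inhaled steroids and "drugs that may have therapeutic effects against COVID-19" are prohibited from consent to the last observation, with no distinction between arms.
- **Table 1 with its footnotes, and Data Collection Items and Management.** These foresee suspension before day 8, including for pneumonia, with a CT at that time. No arm is named.

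**The concern.** A full analysis set should keep randomised patients in their allocated arms, so that the primary comparison retains the protection of randomisation. A per protocol set then shows how far the result depends on adherence. Here the condition that should separate the two sets sits in both definitions.

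This has two consequences. First, the agreement between primary and reference analyses that a reader would take as reassurance is automatic. Second, membership of the primary set depends on events after randomisation. A patient who worsens may receive a prohibited drug or stop trial treatment early, and either may count as a violation. If such patients are lost in unequal proportions from the two arms, the exacerbation rates being compared no longer come from comparable groups.

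**Working it through.** **1. Do the two sets differ?** Let R be the randomised patients with a baseline CT and V those with a serious protocol violation. The full analysis set is R without V. The per protocol set is the full analysis set without V, which is again R without V. The sets are identical provided that serious protocol violation means the same in both sentences.

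**2. Which exclusions arise after randomisation, and in which arm?**

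| Listed violation | Timing | Arm |
|---|---|---|
| Selection or exclusion criteria | Before randomisation | Both |
| Prohibited drug or treatment | Can be after | Both |
| Compliance below 90% | After | Ciclesonide only, since control has no scheduled trial drug |

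**3. The compliance threshold.** There are 3 × 7 = 21 scheduled administrations, and 0.90 × 21 = 18.9. Missing 2 gives 19/21 = 90.5%, so the patient stays in. Missing 3 gives 18/21 = 85.7%, so the patient is out. Three or more missed administrations, about one day, are needed. Early suspension triggers the rule only if compliance is counted against all 21 planned administrations; the document does not state the denominator.

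**4. The plan's own sample size.** Inputs from the Sample Size section are 35% v 10%, two-sided α 10% and power 80%. With mean rate 0.225:

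n₀ = [1.645·√(2 × 0.225 × 0.775) + 0.842·√(0.35 × 0.65 + 0.10 × 0.90)]² / 0.25² = 33.4 per arm.

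With continuity correction, n = (n₀/4)·[1 + √(1 + 4/(n₀ × 0.25))]² = 41.05, rounded up to 42 per arm, or 84 in total. This matches the stated 84. The target of 90 leaves 6 patients (6/90 = 6.7%), meant for withdrawal and dropout. Exclusions for violations would draw on the same 6.

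**5. What exclusions could do (scenarios).** Assume no true effect, a 35% event rate in both arms, 45 per arm, and the Fisher test at two-sided 10%. If a share f of an arm's events is excluded and no non-events are, the apparent rate is 0.35(1 − f)/(1 − 0.35f). The shares f are assumptions; the document gives none. The last column is from 20,000 simulated trials per row.

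| Events excluded, control | Events excluded, ciclesonide | Apparent rate, control | Apparent rate, ciclesonide | Risk ratio | False result favouring ciclesonide |
|---|---|---|---|---|---|
| 0 | 0 | 35.0% | 35.0% | 1.00 | about 3% |
| 0 | 10% | 35.0% | 32.6% | 0.93 | about 6% |
| 0 | 25% | 35.0% | 28.8% | 0.82 | about 12% |
| 0 | 50% | 35.0% | 21.2% | 0.61 | about 35% |
| 25% | 25% | 28.8% | 28.8% | 1.00 | about 4% |
| 25% | 50% | 28.8% | 21.2% | 0.74 | about 15% |
| 33% | 20% | 26.5% | 30.1% | 1.14 | about 2% |

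The nominal level in the favourable direction is 5%. The last row shows the sign reversing: 30.1 − 26.5 = 3.6 percentage points against ciclesonide.

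**The case against.** A reader might infer that the rule removes worsening patients mainly from the ciclesonide arm, and so biases the trial towards benefit. The documents do not support that:

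- Early suspension is foreseen without naming an arm.
- The prohibited drugs apply to both arms. In an open-label trial, worsening control patients might receive them more often.
- The compliance denominator after suspension is not stated. If only administrations due up to suspension count, stopping for pneumonia is not poor compliance.
- The endpoint compares the day 8 CT with day 1. A patient whose exacerbation first appears on day 8 can be fully compliant and stay in. Patients are also hospitalised throughout dosing.
- The CT required at early suspension suggests that these outcomes were meant to be used.

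All of this stands. It means that the rows removing ciclesonide events alone are one-sided scenarios and not an estimate of bias.

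It can also be said that naming the per protocol analysis a separate reference implies that a broader full analysis set was intended, and that the full protocol may define a serious violation more narrowly. That is possible, but the article gives one term and one list. Even under a narrower meaning, its primary set would still exclude randomised patients for violations that it does not specify.

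**Conclusion.** The point holds as a defect of definition. As written, the primary efficacy set equals the per protocol set, the reference analysis is empty, and no efficacy analysis of all randomised patients as allocated is specified. This rests on serious protocol violation having the same meaning in adjacent paragraphs, the only reading that the article offers.

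The effect on the result is a possibility of unknown direction and size. One criterion acts on ciclesonide alone and could be tied to the outcome if compliance is counted against all 21 administrations; others can remove worsening patients from either arm. Across the scenarios, false favourable results range from about 2% to about 35%, depending wholly on the assumed shares excluded from each arm. The definition decides who enters the primary comparison, so it should be corrected before the analysis.

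**What to change.** Delete the no-serious-violations condition from the full analysis set. Define that set as all randomised patients with a baseline CT, analysed by assigned arm regardless of compliance or concomitant drugs. The baseline CT is scheduled for day 1 and the Participant Timeline section places randomisation at day 2, so this condition precedes allocation. Apply the violation list only to the per protocol set and label that analysis as sensitivity.

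The cost is one sentence, carried through to the statistical analysis plan. No data or patients are added, and the required 84 and target 90 stand. The change does not settle how patients without a follow-up CT are handled: the article rules out imputation, so they could still drop out of the primary comparison.

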### Provisions of Posttrial Care

The expected research participation period will last for approximately 1 month, after consent acquisition (ie, 1 week for the protocol treatment period and 3 weeks for the follow-up period). Research participants will be hospitalized during the treatment period, and outpatient follow-up observations will be permitted following the end of the protocol treatment period. In cases where the research participants experience adverse events linked to the treatment, follow-up examinations are to be conducted until the principal physician or subphysician has ensured the safety of the research subject.

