### Outcomes

#### Primary Outcome Measure

The primary outcome is the pneumonia exacerbation rate within 7 days after ciclesonide inhalation. Computed tomography (CT) images taken prior to drug administration and 1 week following treatment will be compared, and efficacy will be confirmed by checking for pneumonia exacerbation. Pneumonia exacerbation will be independently diagnosed by 2 radiologists, who will only refer to the CT images. An exacerbation of pneumonia will be diagnosed if evidence of exacerbation is present on the day 8 CT image compared to the day 1 CT image.

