^a^Leukocyte count, neutrophil count, lymphocyte count, hematocrit level, hemoglobin level, platelet count, and blood sedimentation are to be measured for the hematologic tests.

^b^Albumin, bilirubin, aspartate transaminase, alanine transaminase, lactate dehydrogenase, γ-glutamyl transpeptidase, alkaline phosphatase, creatinine kinase, creatinine, blood urea nitrogen, sodium, potassium, C-reactive protein, glutamic acid, and procalcitonin levels are to be measured for biochemical blood inspections.

^c^Hepatitis B surface antigens, hepatitis B core antibodies, hepatitis C virus antibodies, and HIV antibodies are to be measured for infectious disease inspections.

^d^Prothrombin time, activated partial thromboplastin time, fibrinogen level, and D-dimer level are to be measured for coagulation tests.

^e^For coronavirus inspections, SARS-CoV-2 real-time polymerase chain reaction samples are to be collected with nasal swabs and measured on the day of and 8 days after hospitalization, and serum SARS-CoV-2 antibodies are to be measured on the day of and 8 days after hospitalization.

^f^Chest computed tomography scans are to be taken on the day of and 8 days after hospitalization, and simple chest radiographs are to be taken 4, 8, 15, 22, and 29 days after hospitalization. In addition, image inspections will be conducted as necessary when symptom exacerbation is suspected. Simple chest radiographs on days 22 and 29 will not be taken if the research subject is already discharged. Computed tomography is to be performed when pneumonia worsens within 8 days of hospitalization and when the research is suspended.

^g^Peak expiratory flow is to be measured every morning with a peak flow meter during hospitalization and recorded in a diary.

^h^To be conducted prior to assessment by the physician (eg, before the examination).

^i^Information on drug and treatments other than the trial drug are to be collected.

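### As worded, the full analysis set already excludes serious protocol violators, so it coincides with the per protocol set and the primary analysis drops randomized patients for events after randomization

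*Protocol article*

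**What the plan says.** Under Analysis Sets, the full analysis set consists of registered, randomized patients who "have had their baseline CT image data acquired, and have no serious protocol violations". The per protocol set is defined as "research participants from the full analysis set after removing cases with the following serious protocol violations". The list that follows covers selection and exclusion criteria violations and "prohibited drug violations, prohibited treatment violations, and a medicine administration compliance of below 90" percent. No other list of serious violations appears. The section on discontinuation criteria mentions serious or continuous violations, but only as a reason to review the whole trial.

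Under Statistical Methods for Primary and Secondary Outcomes, the rule for efficacy is: "the full analysis set analysis will be set as the primary analysis, and the per protocol set analysis will be conducted as a reference".

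Three other statements decide what the listed violations mean in practice:

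- **Concomitant care:** "The following drugs are prohibited during the research implementation period (ie, from consent acquisition to the final observation date". The list that follows includes systemic steroids and drugs with possible effect on COVID-19. No rescue exception is stated.
- **Duration (Provisions of Posttrial Care):** "1 week for the protocol treatment period and 3 weeks for the follow-up period".
- **Primary outcome:** a patient has the event if "evidence of exacerbation is present on the day 8 CT image compared to the day 1 CT image".

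Under Interventions, only the ciclesonide group receives the trial drug. Controls receive antitussives and antipyretics as needed.

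**The concern.** A full analysis set is meant to keep patients in the arm to which they were randomized, whatever they later took or missed. Here its definition carries the same condition that the per protocol set uses to remove patients. If that condition is applied as written, the planned contrast between a primary and a reference analysis disappears, and the primary analysis becomes a per protocol analysis.

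This matters because several listed violations arise after randomization and can be linked to the outcome.

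- The drug ban runs for about three weeks past the day 8 endpoint. A patient whose day 8 CT shows exacerbation, and who is then given a banned drug, already has the primary event and could still be excluded.
- Compliance below 90% with the trial drug can occur only under ciclesonide. A ciclesonide patient who worsens and stops inhaling could be excluded, with no counterpart among controls.

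The blinded CT reading, which the Discussion offers as protection against open-label bias, does not help once the patient is outside the set.

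**Working it through.** **1. Set logic.** Let R be randomized patients with a baseline CT and V the listed serious violators.

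- Full analysis set, as written: R minus V.
- Per protocol set, as written: (R minus V) minus V = R minus V.

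The two sets are identical. The second definition is redundant, because nobody is left to remove.

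**2. How strict the compliance limit is.** Three administrations a day for 7 days is 21. Counted by administration (the article does not say how compliance is counted), 90% of 21 is 18.9. Nineteen taken (90.5%) passes and 18 taken (85.7%) fails, so one missed day is enough.

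**3. The plan's own sample size.** Inputs from Sample Size: 35% vs 10%, two-sided alpha 10%, power 80%. The pooled rate is 0.225.

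- Uncorrected: n = [1.645 × √(2 × 0.225 × 0.775) + 0.842 × √(0.35 × 0.65 + 0.10 × 0.90)]² / 0.25² = 33.4 per arm, or 34.
- With continuity correction: (33.4/4) × [1 + √(1 + 4/(33.4 × 0.25))]² = 41.05, or 42 per arm. The total is 84, as stated.
- Exact power of the two-sided Fisher test at 10% with 45 per arm, ignoring the interim look: 0.852.

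**4. Effect of outcome-linked exclusion when ciclesonide does nothing.** Assumptions: true rate 35% in both arms, 45 randomized per arm, two-sided Fisher test at 10%, no interim look. Each exacerbating patient is removed from numerator and denominator with probability L. The documents give no value for L. The expected rate among those kept is 0.35(1 − L)/(1 − 0.35L). Results are from exact enumeration.

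| Assumed loss | Expected ciclesonide rate | Expected control rate | Chance of a false result favouring ciclesonide |
|---|---|---|---|
| None | 35.0% | 35.0% | 3.1% |
| 20% of ciclesonide exacerbators only | 30.1% | 35.0% | 9.9% |
| 25% of ciclesonide exacerbators only | 28.8% | 35.0% | 12.4% |
| 25% of exacerbators in both arms | 28.8% | 28.8% | 3.8% |

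With 0.35 × 45 = 15.75 expected exacerbators per arm, losses of 20% and 25% are about 3 and 4 patients.

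**5. Cost of keeping everyone.** Suppose a share d of ciclesonide patients keeps the control risk. The ciclesonide rate is then 0.10(1 − d) + 0.35d.

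- d = 5%: 0.1125, power 0.804.
- d = 10%: 0.125, power 0.751.

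Both compare with 0.852 at d = 0.

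**The case against.** The strongest reply is that the intended meaning is benign. Speaking of removal from the full analysis set, and calling the result a reference, makes sense only if listed violators are still in that set. The condition in the full analysis set would then refer to some narrower class. The article condenses a fuller protocol, which may define that class, as may the analysis plan. This stands as a reading of intent. It does not remove the point, because the article uses the same term in both definitions and lists its content only once. The problem is a stated rule, not an omitted detail.

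A reader might infer that the two definitions contradict each other. They do not: both can be applied, and the second then has no effect.

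A reader might also infer that patients with the event will be lost in numbers that bias the trial. The documents do not support that either.

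- Many CT-defined exacerbations in mild patients may need no banned drug.
- No text says outright that a drug given after day 8 cancels an outcome already observed. This follows only from combining the length of the ban with the literal set definition.
- For worsening before day 8, the Table 1 footnote on imaging states: "Computed tomography is to be performed when pneumonia worsens within 8 days of hospitalization and when the research is suspended". The ban may end at suspension, and the article does not settle this.
- If losses were equal in the two arms, the false-positive risk would hardly move (3.8% against 3.1%).

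**Conclusion.** The point holds as a defect of wording with a possible consequence for validity. As written, the primary efficacy set equals the per protocol set and excludes randomized patients for post-randomization drug use and non-compliance. Two readings are open: one gives a sound primary analysis and the other does not. In an open-label trial the choice should not be made after outcomes and drug use are known.

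The size of any bias cannot be determined from the documents. The risk lies in one-sided loss. If 20% to 25% of ciclesonide exacerbators alone were dropped, the chance of a false result favouring ciclesonide would be roughly three to four times the 3.1% without loss, and above the nominal 5% per side. These loss shares are assumptions, and the calculation ignores the interim look. The plan should be corrected, but nothing here shows that its result would be wrong.

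**What to change.** In Analysis Sets, delete the last condition of the full analysis set definition, the one on serious protocol violations. The set is then all randomized patients with a baseline CT, analysed as randomized regardless of later drug use or compliance. Keep the violation list for the per protocol set only.

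Make the change before the interim efficacy look at 50% enrollment, which tests the same primary endpoint. If that has passed, make it before anyone choosing the set has seen outcomes by arm, and record the date.

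The change needs no new visits or scans and leaves the target of 90 as it is. Its cost is dilution by non-adherent patients: if 5% or 10% of ciclesonide patients (assumed) kept the control risk, power would be about 0.80 or 0.75 instead of 0.85. The per protocol analysis remains available as the reference for that question. This fix requires no change to the prohibited-drug rule or the definition of the primary outcome.
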